### Study Design

A multi-site RCT design is adopted. All the 24 ICCMWs will be invited to join this research. Assuming a conservative response rate of 60–70%, about 14–17 ICCMWs will join. At each site, a pair of intervention (brief daily BMS group) and control groups (tea break group) will be run. Each group will have about 10 participants. Thus, there will be a totally about 280–340 participants randomly assigned to either an intervention or control group. The study will be registered with the Clinical Trials Centre of The University of Hong Kong.

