### Participants and Sample Size Calculation

In light of the findings of the pilot trials, an effect size is assumed at a moderate level of 0.4. For a 2-arm RCT with power at 90%, significance level at 0.05, and allowing for a 10% attrition rate (dropout rate in pilot studies was zero), a sample size of 75 per arm is needed (G^∗^Power software version 3.1, Franz Faul, University of Kiel, Germany). Totally 150 participants will be required. Assuming an average of around 8 participants per group, a total of 9 pairs of intervention and control groups will be needed. Each study site, an ICCMW, will host a pair of intervention and control groups. Thus, a totally 9 study sites are needed.

The other consideration is the variability among the 24 ICCMWs in Hong Kong. They are run by 11 NGOs with a rather diversified background. For example, some of these NGOs are more experienced in mental health services, and some are bigger and more well-established. To reduce the bias at the study-site level, instead of only randomly selecting 9 of them, we aim to invite all the 24 ICCMWs to participate in the study. Assuming a conservative response rate of 60%, about 14 ICCMWs will join. At each site, a pair of intervention and control groups will be run. Each group will have about 8 participants. Thus, there will be a totally about 224 participants randomly assigned to either an intervention or a control group.

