### Data Analysis

Both completers and intention-to-treat analysis will be performed. In the intention-to-treat analysis, missing data will be handled by ‘last observation carried forward.’ With a 2-arm RCT design, the efficacy of the intervention will be examined by repeated measures MANOVA on both primary and secondary outcome variables. Partial eta-squared (η^2^) values are computed to assess the effect sizes; values of 0.02, 0.13, and 0.26 suggest small, medium, and large effect sizes, respectively (Pierce et al., 2004). To investigate within group effects, serial trend analysis from T0 to T6 will be conducted on the outcome variables. In the case of work engagement, changes in a range of scores from T0 to T6 will also be examined. The associations between primary and secondary outcome variables will be explored by correlational and multiple regression analyses.

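### Both arms are delivered in small daily groups, but neither the sample size nor the named MANOVA allows for within-group correlation; if it is present, the arm comparison is anticonservative and power is overstated.

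*Protocol article*

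**What the plan says.** - **Design.** Under Recruitment Strategy, consenting workers at each centre are allocated individually, 1:1. Study Design adds: "At each site, a pair of intervention (brief daily BMS group) and control groups (tea break group) will be run". Procedures has each group meeting every workday for 3 months. BMS groups have a facilitator chosen from their own members (Intervention); tea-break groups have a coordinator.
- **Sizing.** Participants and Sample Size Calculation takes as its inputs "an effect size is assumed at a moderate level of 0.4" and "For a 2-arm RCT with power at 90%, significance level at 0.05, and allowing for a 10% attrition rate", and concludes that "a sample size of 75 per arm is needed". Group size enters only to turn a head count into a number of sites: "Assuming an average of around 8 participants per group" gives 9 pairs. The planned recruitment is then raised to 14 sites and 224 workers. The reason given begins "The other consideration is the variability among the 24 ICCMWs in Hong Kong" and concerns bias between sites, not correlation within groups.
- **Analysis.** Data Analysis says "the efficacy of the intervention will be examined by repeated measures MANOVA on both primary and secondary outcome variables". It mentions no site term, group term, random effect or cluster-robust error.

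**The concern.** Randomising individuals does not make outcomes independent when treatment is then given in fixed groups. A BMS group shares one facilitator, who may choose the practices, and has daily discussion and activities meant to build mutual care. The tea break is there to control for social gathering, and the Background argues that one worker's attitude affects colleagues and team morale. On the plan's own reasoning, group members influence each other's burnout and engagement, in both arms.

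The two levels act differently:

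- **Group (site by arm).** Variation between groups does not cancel in the arm contrast. Leaving it out makes standard errors too small.
- **Site.** Every site hosts both arms, so a shared site effect cancels. Leaving it out puts site variance into the error term and makes the test slightly conservative.

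At stake are the error rate of the main efficacy test and the power claimed for it.

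**Working it through.** **Inputs from the article:** effect size 0.4, power 90%, alpha 0.05 (taken as two-sided), 10% attrition, 8 per group, 14 pairs, so 14 × 8 = 112 per arm and 224 in total. **Assumed, because the article gives none:** group ICC of 0.02, 0.05 or 0.10.

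**1. The plan's own figure.** Two independent arms need n = 2 × ((1.960 + 1.282)/0.4)² ≈ 131 per arm, or 133 with the t distribution. Dividing by 0.9 gives 148. The stated 75 does not reproduce for a two-arm comparison; 75 analysed per arm gives about 68% power. A paired or one-sample t-test (68, times 1.1 = 75) does match it. This is a separate defect. It matters here because the power figures below start from the planned 112 per arm, not from the claimed 90%.

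**2. Net variance factor.** Set the total variance to 1, with share ICC_group between groups within a site and ICC_site between sites. The true variance of the arm difference, relative to that of an independence analysis, is about

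1 + (m − 1) × ICC_group − ICC_site.

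With m = 8 this exceeds 1 when ICC_group is more than one seventh of ICC_site.

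**3. Illustration for one time point, ICC_site = 0.** Design effect DE = 1 + 7 × ICC. Type I error = 2 × (1 − Φ(1.96/√DE)). Power = Φ(0.4/√(2 × DE/112) − 1.96).

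| Group ICC | DE | Type I error | Power, 112 per arm |
|---|---|---|---|
| 0 | 1.00 | 5.0% | 85% |
| 0.02 | 1.14 | 6.6% | 80% |
| 0.05 | 1.35 | 9.2% | 73% |
| 0.10 | 1.70 | 13.3% | 63% |

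The power column is for an analysis that carries the correct variance, with large degrees of freedom.

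**4. With 10% attrition.** About 7.2 per group, or 101 per arm, remain. DE is 1.12, 1.31 and 1.62, and power falls from 81% to 76%, 70% and 61%. Tested on 13 degrees of freedom (14 site pairs), it is 70%, 63% and 54%.

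**5. Adding a site effect.** With ICC_site = 0.05 and no group effect, the factor is 0.95 and type I error is about 4.4%. With group ICC 0.02, 0.05 and 0.10 the factor is 1.09, 1.30 and 1.65, giving about 6.0%, 8.6% and 12.7%. The site offset is small.

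**6. Simulation check.** With 14 pairs of groups of 8 and no site effect, a naive two-sample test rejected in 6.5%, 9.1% and 13.6% of null trials at the three ICCs. A site-paired analysis of group means stayed close to 5% (4.9% to 5.4%).

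**The case against.** - **The article lists no model terms.** Site could enter a MANOVA as a between-subject factor, and a fuller plan may say so. This stands for site: it is not stated, which is not the same as excluded. It does not stand for the group. The named method has no random group effect, and the sizing text is complete enough to show that no design effect was used.
- **The direction is not certain.** A reader might infer that standard errors are necessarily too small. The documents do not support that without a condition: a shared site effect pulls the other way, and no ICC is given. The condition, a group ICC above one seventh of the site ICC, is weak and plausible here.
- **The planned test is different.** A reader might take 9.2% or 13.3% as the true error rate of this trial. They are figures for a two-sample comparison at one time point. In the planned repeated measures analysis from T0 to T6 the evidence would normally be the arm-by-time effect. Workers are individually randomised, so no treatment-group effect exists at T0, and the relevant ICC is that of change. The independence assumption is the same, but the figures are illustrative.
- **The surplus could absorb it.** Were 75 per arm right, 112/75 = 1.49 would cover a group ICC up to about 0.49/7 = 0.07. But 75 does not reproduce, so that margin is not there. Extra recruitment also cannot repair the type I error of an independence analysis.
- **Other group sizes.** Study Design gives about 10 per group. At that size and 14 sites, power at ICC 0.05 is better (79%), but type I error is worse (10.4%).

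**Conclusion.** The point holds in conditional form. The article fixes an individual-level sample size and names an analysis without a group-level error term for a treatment given in groups in both arms. If outcomes correlate within groups by more than about one seventh of the site ICC, the efficacy test is anticonservative. Over an assumed group ICC of 0.02 to 0.10, the illustrative type I error runs from 6.6% to 13.3%, and power at the planned 224 from 80% to 63% (76% to 61% with attrition, lower on 13 degrees of freedom).

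A reader might also put the whole gap between the claimed 90% and these values down to clustering. That is not supported: without any clustering, 112 per arm already gives only 85% (81% with attrition), because 75 per arm does not reproduce. Only the further fall belongs to this point.

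**What to change.** **Analysis.** Replace the repeated measures MANOVA by a linear mixed model with fixed effects for site, arm, visit, arm by visit and baseline score; random effects for group (site by arm) and participant; and small-sample degrees of freedom such as Kenward-Roger. A site-paired analysis of group means is an equally valid and simpler alternative.

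**Sample size.** State an ICC range with its justification, show the design effect for the intended group size, and give the power of the planned 224 over that range.

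**Cost.** Changes to the analysis wording and the sample-size text, somewhat wider intervals and a lower stated power. Randomisation, treatment delivery and data collection stay as they are, provided each worker's group is recorded in the data set.

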### Procedures

In order to examine the course of changes in burnout and engagement, the intervention period is extended from 1 month in pilot trials to 3 months in the proposed study. The post-intervention follow-up period is also extended to 3 months. Measures will be taken at baseline (T0), and then at monthly intervals (T1–T6). All questionnaire surveys will be administered by the research assistant of the study.

According to the experience of pilot trials, frontline professionals such as social workers, occupational therapists and nurses are good facilitators for the intervention groups. A 1-h training session suffices in introducing new facilitators to the intervention. A member of the research team will sit-in the meetings of each new group in the first week, and provide feedback to the facilitator. Afterward, to ensure treatment fidelity, a member of the research team will visit the group biweekly, until the end of intervention.

During the 3-month intervention period, the trained facilitator will run the brief daily BMS group in a quiet room at the site every workday, normally 5 times a week except when there are public holidays. At each site, the facilitator and participants may decide on their preferred time slot on a day for the BMS group that fits their work schedule. It can be in the morning, at noon or in the afternoon, and the exact meeting time can be changed during the 3-month intervention period if the group prefers. The facilitator will keep an attendance record of participants for statistical purpose.

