### Outcomes Measures

Measures of the related variables are summarized in Table 1 below. In line with the study’s objectives, primary outcome variables are work burnout and engagement. Since the intervention adopts a multidimensional BMS orientation, multiple somatic complaints, positive and negative affect, and daily spiritual experience are included as secondary outcome variables. Also included as secondary outcome variables are worker behavior, including overtime hours, sick leave, and injuries at work.

**TABLE 1 T1:** Variable table.

**Variable/instrument**	**Content of the instrument**	**Data type**

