**Secondary outcome variables**		
**(1) Multiple somatic symptoms** ◆ Physical Distress subscale of the Body-Mind-Spirit Well-Being Inventory (Ng et al., 2005)	14-item self-report scale	Interval
**(2) Positive affect** ◆ Positive Affect subscale of the Body-Mind-Spirit Well-Being Inventory (Ng et al., 2005)	8-item self-report scale	Interval
**(3) Negative affect** ◆ Negative Affect subscale of the Body-Mind-Spirit Well-Being Inventory (Ng et al., 2005)	11-item self-report scale	Interval
**(4) Daily spiritual experience** ◆ Chinese Daily Spiritual Experience Scale (Ng et al., 2009a)	16-item self-report scale	Interval
**(5) Collective psychological ownership** ◆ Chinese Collective psychological ownership Scale (Ng and Su, 2018)	7-item self-report scale	Interval
**(6) Worker behavior** ◆ Self-report items	Overtime hours, sick days taken off from work and injuries at work in the past month	Interval and ordinal

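### Past-month sick days, injuries and overtime are committed to repeated measures MANOVA with last observation carried forward, a rule that has no sound meaning for a monthly tally and may leave a weak test

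*Protocol article*

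**What the plan says.** The Data Analysis section of the protocol article fixes one efficacy method for every outcome: "the efficacy of the intervention will be examined by repeated measures MANOVA on both primary and secondary outcome variables". It plans two analysis sets, "Both completers and intention-to-treat analysis will be performed", and ties the missing-data rule to the second of these: "In the intention-to-treat analysis, missing data will be handled by ‘last observation carried forward".

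The Outcomes Measures section brings worker behaviour under that rule: "Also included as secondary outcome variables are worker behavior, including overtime hours, sick leave, and injuries at work". Table 1 defines the items as "Overtime hours, sick days taken off from work and injuries at work in the past month", collected by self-report, and gives their data type as "Interval and ordinal" without saying which item is which. They are collected seven times, per the Procedures section: "Measures will be taken at baseline (T0), and then at monthly intervals (T1–T6").

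No other efficacy model is named for these three items. The article does not say whether the group term or the group-by-time term of the MANOVA is the efficacy test. It gives no event rate, distribution or power for any of them.

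**The concern.** A rating-scale score describes a state that might persist, so carrying it forward is at least an intelligible assumption. A past-month tally describes one closed month. Five sick days in one month are not an observation about the next, and neither is a month with none. Carry-forward nevertheless records either value as if the worker had reported it.

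The model raises a second question. Table 1 types part of this outcome as ordinal, while MANOVA treats every outcome as continuous. Monthly sick days and injuries in full-time staff are plausibly mostly zeros, although the article gives no rates. A six-degree-of-freedom test of monthly change may then detect little, and with very rare injuries it may not be computable.

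At stake is how a null result on sick leave or injuries is read. These are the only work-behaviour outcomes; apart from demographics, the rest are rating scales. A null result could reflect the test and the missing-data rule rather than the programme.

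**Working it through.** **Inputs from the article.** Seven visits (T0–T6), intervention over T1–T3, about 224 participants at 1:1 (112 per arm), and 10% attrition, which leaves 224 × 0.9 ≈ 202, or 101 per arm. The article has no figure for these outcomes to reproduce: its power statement concerns a standardised effect of 0.4 and does not mention them. **All event rates and dispersions below are assumptions.** Clustering by site and group is ignored.

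**1. What carry-forward enters.** A worker who reports 5 sick days at T2 and then leaves is given 5 at each of T3, T4, T5 and T6, or 4 × 5 = 20 unreported days. A worker who reports 0 at T2 and leaves is given four unreported zeros. The error runs both ways.

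**2. Size under random dropout.** If 10% leave at times spread evenly over T1–T6, the average leaver misses 3.5 of 6 months, so the imputed share is 10% × 3.5/6 = 5.8%. A simulation with 112 per arm, 0.5 sick days per month and a sustained rate ratio of 0.7 gave 34.3 carried days against 32.9 true days in the missing months. The expected total is 112 × 6 × (0.50 + 0.35) = 571, so carried days are 34.3/571 = 6.0% of it. For injuries (0.05 per month, same rate ratio) it was 3.6 carried against 3.4 true. MANOVA power was 9.8% with dropout and carry-forward and 10.7% without dropout.

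**3. Size when dropout follows a bad month.** In a deliberately extreme case (about 8–9% dropout, only after months with 3 or more sick days), carried events were 2.5 to 4.5 times the true missing events. This is a bound, not a forecast.

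**4. Power, if group-by-time is the test.** 101 per arm with complete data, so no carry-forward. Sick days are Poisson with gamma person and visit effects (shape 0.5 each), giving 71–84% zeros, and the effect is confined to T1–T3. Three tests are compared:
- Hotelling T² on the six changes from T0, which is the two-arm group-by-time MANOVA
- normal-theory ANCOVA on the T1–T3 total, adjusted for T0
- log-link Poisson model with robust variance on the same total, adjusted for T0

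| Mean per month | Rate ratio | MANOVA, 6 df | ANCOVA on total | Count model |
|---|---|---|---|---|
| 0.3 | 0.6 | 10% | 34% | 40% |
| 0.3 | 0.5 | 17% | 53% | 60% |
| 1.0 | 0.6 | 15% | 45% | 52% |
| 1.0 | 0.5 | 24% | 68% | 74% |

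Null rejection was 2–5% for MANOVA, 5–6% for ANCOVA and 7–10% for the count model.

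**5. Where the loss comes from.** The share of the gain that ANCOVA alone recovers is (ANCOVA − MANOVA)/(count − MANOVA): 24/30 = 80%, 36/43 = 84%, 30/37 = 81% and 44/50 = 88%. Gaussian data with the same means and covariances gave the same MANOVA power as the counts (11% v 11%; 112 per arm, 0.5 per month, rate ratio 0.7 sustained). The focused, baseline-adjusted contrast therefore explains most of the difference.

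**6. Overtime.** At an assumed 10 hours per month, rate ratio 0.7, 112 per arm and 10% dropout, MANOVA against the count model was 44% v 98% for a sustained effect and 78% v 78% for one fading after month 3. The loss is not general.

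**7. Can MANOVA be computed for injuries?** The six-contrast covariance matrix becomes singular once two of the seven visits have no injury at all. At an assumed 1% per month with person-level gamma variation (shape 1), the chance of an empty visit among 202 people is 1.01^−202 = 0.134. The chance of two or more empty visits in seven is 1 − 0.866^7 − 7 × 0.134 × 0.866^6 ≈ 24%. With the intervention rate halved at T1–T3 it is about 34%. Simulation gave 25–26% and 35–36%. At 2% per month it was 1–3%, and at 5% it did not occur.

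**The case against.** The strongest reply is that the power comparison does not indict MANOVA for counts. Normal-theory ANCOVA on the period total recovers 80–88% of the gain, and the count model's last 5 to 8 points come with null rejection of 7–10%. The article also does not name group-by-time as the efficacy term. All of this stands, and it limits the power argument to a conditional one.

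A reader might infer that normal theory and carry-forward together lose most of the power and invent events. The documents do not support that. The power loss comes mainly from the unfocused test, carry-forward barely moves power under random dropout, and it enters zeros as well as events. A reader might also infer that the MANOVA assumptions certainly fail, or that overtime is the ordinal item. The article gives no rates, and Table 1 does not say which item is ordinal.

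The planned completers analysis uses no carry-forward. It is no repair, however, because it drops the same people whose leaving may be related to sick leave or injury. Finally, these items appear in no objective, in none of H1–H4 and not in the sample size. That is right, and it caps the severity.

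**Conclusion.** The point holds in a limited form, at minor to moderate severity. The article states a method and a missing-data rule for these items, so this is a poor stated choice and not a detail left to another document.

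The firm part needs no assumed rates: carrying a past-month tally forward has no sound meaning. Its net effect is small under random dropout at 10%, and it can bias the comparison if leaving follows a bad month or differs by arm.

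The conditional part is power. If group-by-time is the test, power for a 40–50% cut in sick days at T1–T3 is about 10–24%, against 34–68% for ANCOVA on the T1–T3 total and 40–74% for a count model with somewhat high null rejection. Non-computability arises for injuries only if they are as rare as about 1% per month, and then in a quarter to a third of trials. Both rest on assumed rates and dispersion and ignore clustering.

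**What to change.** Amend the Data Analysis section for these three items:

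- Do not carry sick days, injuries or overtime forward.
- For sick days and injuries recorded as counts, compare arms on the observed T1–T3 total, and separately on T4–T6. Use a log-link model (negative binomial, or Poisson with small-sample-corrected robust variance), an offset for months observed, the T0 value as covariate and a site term. Report rate ratios with 95% confidence intervals.
- If injuries prove very rare, compare any versus none over the period.
- State in Table 1 which item is ordinal, and use an ordinal model for that item. If overtime is recorded in hours, compare its period mean with adjustment for T0.
- Name the efficacy contrast for these outcomes.

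The offset stops unreported months being filled in, but it does not by itself remove bias if leaving depends on unreported sick days or injuries. Dropout by arm and by last reported tally should therefore be tabulated.

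The cost is analysis wording only, since the items are already collected monthly. The downside is that these secondary outcomes are reported on a different scale from the MANOVA results.

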We have piloted this brief daily BMS program separately for professional and care workers at elderly services for a duration of 1 month (Ng, 2014). Both qualitative and quantitative findings supported the acceptability and feasibility of the intervention, and its potential efficacy in reducing burnout and fostering sustainable emotional capacity and work engagement. Attendance rate in both groups exceeded 80%. More encouragingly, the dropout rate was zero in both groups. In subsequent focus group meetings, participants shared that they felt revitalized with positive energy after every meeting, and thus could better work with service users at workplace and enjoy the time with family members in the evening. Both the facilitators and participants enjoyed participating in the program and did not see it as an additional burden. Some participants expressed that they actually looked forward to it on every workday during the pilot period, and wished that the program could be continuously offered at their workplace.

The quantitative findings of the pilot trials are also encouraging. Despite a small sample size (totally *N* = 16), reduction in burnout was significant in both groups. Effect size was in the range of moderate magnitude. However, the positive changes at 1 month after completion of the program appeared to diminish. This suggests that a continued or a longer duration program is desirable.

Findings of change in work engagement go beyond the expectation, but perhaps are most inspiring. In the group with a high baseline engagement level (4.0 out of a theoretical range of 0–6; *SD* = 0.8), a significant reduction in engagement was observed, in parallel to a mark reduction in burnout. In the group with an average baseline engagement level (3.0; *SD* = 1.0), no significant change in engagement level was observed, but in parallel, there was also a mark reduction in burnout.

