## Research Methods and Design

### Research Aim and Objectives

The overall aim of the proposed research is to pursue the further rigorous trial of the brief daily BMS program, which demonstrated good potentials in the pilot studies. The specific objectives are:

(1)To evaluate the efficacy of the brief daily BMS program in reducing burnout and enhancing engagement for community mental health workers;(2)To examine the trajectory of burnout, especially exhaustion, during a 3-month intervention and 3-month post-intervention periods; and(3)To examine the trajectory of engagement during a 3-month intervention and 3-month post-intervention periods.

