### Hypotheses

In light of the literature and findings of the pilot trials, we have the following hypotheses:

H1: Reduction of burnout will be observed within the 3-month intervention period;H2: Rebound of burnout will be observed within the 3-month post-intervention period;H3: A narrowing of range in work engagement will be observed within the 3-month intervention period; andH4: A widening of range in work engagement will be observed within the 3-month post-intervention period.

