### Theoretical Implication

At the theoretical level, this study will contribute to answering the debate whether intervention with self-awareness/mindfulness component can reduce burnout significantly. Self- awareness/mindfulness interventions demonstrated a promising effect to reduce work related stress (Strauss et al., 2018). However, the results of these interventions on burnout are equivocal. Significant improvement of burnout has not been observed in some previous studies (Cohen-Katz et al., 2005; Janssen et al., 2018). This may be partly because the widely used measure, Maslach Burnout Inventory (Maslach et al., 1996) cannot capture the core components of burnout (Lomas et al., 2017). The proposed study will adopt the Copenhagen Burnout Inventory – Chinese Version, which has been revealed to show satisfactory validity and reliability (Fong et al., 2014). The results of our study will contribute to the evaluation of burnout relief from self-awareness/mindfulness interventions.

Besides, the study will reveal a new understanding of work engagement. Our pilot trials revealed reduction of exceptional high engagement alongside with reduction in burnout. Previous studies mentioned above also show that if the engagement level is “too high,” it may undermine individual wellbeing as well as organizational performance. Therefore, engagement may be like ‘fire’ fueling us at work, but it can ‘burn’ if it is overly strong. This study is expected to reveal an optimal range for work engagement: high enough for good performance, low enough to avoid burnout. Furthermore, because engagement consists of three components: passion, vigor, and absorption, the multidimensional analysis may shed light on the effect of each component of work engagement.

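### Engagement, a primary outcome, has conflicting success criteria: the objective and the efficacy test concern its level, while H3 and H4 concern its spread, which gets no clear between-arm test

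*Protocol article*

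**What the plan says.** The protocol article's Outcomes Measures section states that "primary outcome variables are work burnout and engagement". The first objective is "To evaluate the efficacy of the brief daily BMS program in reducing burnout and enhancing engagement for community mental health workers"; the third is to follow the trajectory of engagement over the intervention and post-intervention periods.

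The Hypotheses section contains no statement about the level of engagement. H3 reads "A narrowing of range in work engagement will be observed within the 3-month intervention period", and H4 predicts the reverse in the three months afterwards. The Abstract and Conclusion repeat both.

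The background on the pilot explains why. In the group with high baseline engagement (mean 4.0, SD 0.8), "a significant reduction in engagement was observed, in parallel to a mark reduction in burnout". In the group with average baseline engagement (mean 3.0, SD 1.0), engagement did not change significantly. The authors conclude that the goal is an optimal level, neither too low nor too high.

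The Data Analysis section tests efficacy by repeated measures MANOVA on primary and secondary outcomes, adds a within-group trend analysis from T0 to T6, and then says: "In the case of work engagement, changes in a range of scores from T0 to T6 will also be examined". The sample size rests on a single effect size of 0.4, and none is given for spread.

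**The concern.** The objective and the hypotheses define success on engagement differently. Under Objective 1 the mean should rise. Under H3 the distribution should tighten, and the pilot suggests that this may happen because high scorers come down. The named efficacy test looks only at means.

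A trial that behaves as H3 predicts could thus be reported as no effect on engagement, or as a worsening. Conversely, a raised mean, an unchanged mean or a narrowed range could each be presented as success once the data are known. For a primary outcome, that choice should be closed in advance.

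The only tool named for spread is also a weak one if taken literally, and no comparison with the tea-break group is stated for it.

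**Working it through.** **No plan figure to reproduce.** The article gives no effect size, power or sample size for H3, H4 or any measure of spread. The SD ratios and correlations below are assumptions.

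**Inputs.** The target is about 224 participants at 1:1, so 112 per arm. With the plan's 10% attrition, 112 × 0.9 ≈ 101 per arm. Significance level 0.05, taken as two-sided. Scores are taken as normal, and clustering is ignored.

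**1. What a test of means sees.**
- *Symmetric narrowing.* High scorers fall as much as low scorers rise, so the arm means do not differ and the test rejects at about its error rate. Simulated rejection was about 5% at 101 per arm with SD ratio 0.75, and 4% to 6% across SD ratios 0.7 to 0.9 with 67 to 112 per arm.
- *Only high scorers fall.* If distances above the mean are halved and the lower half is untouched, the mean moves by −0.5 × 0.399 ≈ −0.20 SD (0.399 is the standard normal density at zero), and the SD ratio is about 0.76. With a T0–T3 correlation of 0.6 and 101 per arm, a mean-based comparison rejects in about 36% (change score) to 50% (ANCOVA) of simulated trials, and the shift is downwards, against Objective 1.

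**2. Efficiency of the range.** At n = 101 the simulated coefficient of variation is about 0.122 for the range and 0.071 for the SD. Relative efficiency = (0.071 / 0.122)² ≈ 0.34.

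**3. Power to detect narrowing, between arms at one time point.** On the log scale, power ≈ Φ(|ln ratio| / SE − 1.96).
- SE for the SD: √(1/200 + 1/200) = 0.100.
- SE for the range: √2 × 0.121 ≈ 0.171 (0.121 is from a second simulation run).
- Ratio 0.75, |ln| = 0.288. SD: Φ(2.88 − 1.96) ≈ 0.82. Range: Φ(1.68 − 1.96) ≈ 0.39.
- Ratio 0.80, |ln| = 0.223. SD: Φ(2.23 − 1.96) ≈ 0.61. Range: Φ(1.30 − 1.96) ≈ 0.25.

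Simulation agrees:

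| SD ratio | Range | Brown-Forsythe | Variance ratio |
|---|---|---|---|
| 0.75 | 39–40% | 74–75% | 81–82% |
| 0.80 | 25–26% | 52–53% | 59–60% |

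**4. Same question as change from baseline** (112 per arm, scores bounded 0–6, T0–T3 correlation 0.5 to 0.7).

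| SD ratio | Range | Log SD |
|---|---|---|
| 0.9 | 7% | 15–19% |
| 0.8 | 16–18% | 48–65% |
| 0.7 | 33–38% | 87–96% |

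The levels differ from step 3, but the ordering does not.

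**5. Is a baseline-by-arm interaction a substitute?** No. With slopes of T3 on baseline of 0.2 and 0.6 but equal SDs in both arms, the interaction rejects in about 88% of trials although nothing has narrowed. With true narrowing (SD ratio 0.75) and equal slopes, it rejects in about 5%, against about 74% for Brown-Forsythe. It answers who moves, not whether the spread shrinks.

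**The case against.** The best defence is that the article has several objectives and several analyses. The MANOVA can serve Objective 1 (level), and the trend and range analyses Objective 3 (trajectory). The Abstract and Conclusion frame narrowing as change over time in the intervention participants. The estimator and test for spread may be set out in a fuller document.

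Part of this stands. Silence about a between-arm comparison of spread is not a statement that none will be made, and a range of scores may mean spread in a looser sense. But the article itself fixes the objective, the hypotheses and the efficacy test, and these do not match. Narrowing seen only within the intervention arm cannot be credited to the program when a randomised tea-break group exists for that purpose.

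A reader might go further in four ways that the document does not support:
- *The hypothesis cannot be tested.* A range can be compared between arms, for example by permutation; it is merely inefficient.
- *The engagement test has only 5% power if the program works as hypothesised.* That holds for symmetric narrowing alone. H3 does not say that narrowing is symmetric, and the pilot pattern was not.
- *Dropout will shrink the range and favour H3.* The plan uses last observation carried forward, which keeps the number constant after baseline, and a completers analysis, ordinarily one fixed set. Neither compares a larger T0 sample with a smaller T3 sample.
- *The analysis cannot deliver the optimal range.* The sentence "This study is expected to reveal an optimal range for work engagement: high enough for good performance, low enough to avoid burnout" is an aspiration in the Discussion and a separate matter; multiple regression can carry a curved term.

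**Conclusion.** The concern holds as a mismatch between objective, hypotheses and test for a primary outcome. The mismatch is textual and needs no assumption.

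Its size depends on how engagement changes. The mean-based test has no power beyond its 5% error rate under symmetric narrowing, and points away from Objective 1 if mainly high scorers fall. If the range is maximum minus minimum, it uses about 34% of the information in the SD, which at an assumed SD ratio of 0.75 and 101 per arm means about 39% power instead of about 74%. These figures assume normal scores and independent participants. Clustering by site and group would alter them. At an SD ratio of 0.9, the change-based comparison is weak with either measure.

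**What to change.** 1. Reword Objective 1 so that its aim for engagement agrees with H3 and H4. If the level is also of interest, state it as a separate question with its own direction.
2. Test H3 and H4 by a between-arm comparison of dispersion, either at T3 and T6 or as change from T0 to T3 and from T3 to T6. A ratio of SDs with a Brown-Forsythe test, or a model with arm-specific variances, would serve. Allow for clustering by site and group.
3. Report the range as description only, and define it.
4. A baseline-engagement by arm interaction may be added as a supportive analysis of who moves, not as the test of narrowing.

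The cost is the wording of one objective and a few sentences in the analysis section. All the data are already planned at T0 to T6. The choice should be fixed before outcome data are examined by arm.
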